### Interventions

#### Study medication

Preparation and labeling of doxycycline and placebo will be performed by the Clinical Trials Unit department of the Clinical Pharmacy of the Radboud University Nijmegen Medical Centre, and will be done according to the relevant Good Manufacturing Practice (GMP) guidelines. Study medication will be prepared as capsules with identical appearance. Participants allocated to study medication will be treated at the Q fever outpatient clinic. Participants will receive either doxycycline (200 mg once daily) or placebo (once daily), both orally administered, for a period of 24 weeks. Study medication will be provided by the first author ([name]). For safety considerations all participants in the medication condition will visit the Q fever outpatient clinic 4, 8, and 16 weeks after start of the treatment (see Figure 1). Furthermore, liver enzymes will be checked, and drug utilization will be recorded. Therefore, patients are required to bring the study medication to all visits. In addition, blood samples drawn 8 weeks after start of treatment will be stored by the study pharmacist, who performed the double-blinded randomization. Eventually, doxycycline levels will only be determined in participants receiving doxycycline, and results will be kept secret until the entire study is completed. After completion, it is known whether doxycycline levels were sufficient to sort out effect [32]. Participants will be excluded in case of: serious side effects; aspartate aminotransferase (AST)/alanine aminotransferase (ALT) levels more than 5 times the upper limit of normal; alkaline phosphatase (AF) levels more than 3 times the upper limit of normal; more than 10 days use of antibiotics potentially active against *C. burnetii* (co-trimoxazol, quinolon, macrolides or tetracyclines); or discontinuation of study medication for more than 7 consecutive days.

#### Cognitive behavioral therapy

CBT for QFS is aimed at changing the beliefs and behaviors assumed to maintain fatigue. On average, CBT consists of 12–14 sessions over a period of 24 weeks, and is individually delivered by trained cognitive-behavioral therapists from the ECCF, according to a written treatment manual. The treatment is based on CBT for CFS [33]. First, the model of fatigue perpetuating beliefs and behaviors is explained to patients. At the start of the therapy patients formulate their goals in behavioral terms. These goals usually include the resumption of work, hobbies, and other activities that imply that the patient is no longer severely fatigued and disabled, which is the goal of CBT for QFS. Patients regulate their bedtimes and stop sleeping during the day in order to stop possible disruption of the circadian rhythm. During the sessions, the therapist elicits and challenges patients’ non-accepting and catastrophising beliefs with respect to fatigue. Additionally, patients are taught how to distract their attention from their fatigue. Two groups of patients are discerned: relatively active patients, who are characterized by bursts of activity followed by periods of relative inactivity, and low active patients, who have extremely low activity levels on most days [31]. Relatively active patients first learn how to divide their activities more evenly across the day. Low active patients start with a graded activity program immediately after the initial cognitive interventions. This activity program consists of daily walking or cycling, which is gradually increased. The increase in activity is not determined by the level of symptoms, but is time contingent. When patients succeed in increasing their physical activity, they also start to increase their social and mental activities. In the last phase of therapy, patients work systematically towards reaching their goals, which are formulated at the start of the therapy. Following this, they are encouraged to perceive feelings of fatigue as a normal part of an active and healthy life.

### Post intervention

Twenty-four weeks after start of treatment, all participants visit the ECCF for the end-of-therapy study visit, including assessment of the outcome measures (see Figure 1). Twenty-six weeks after start of treatment, participants visit the Q fever outpatient clinic for the end-of- study visit. During this end-of-study visit, *C. burnetii* serology and PCR will be determined.

### Outcome measures

The primary outcome measure is the fatigue severity measured by the subscale *fatigue severity* (8 items, 7-point Likert Scale) of the Checklist Individual Strength (CIS questionnaire) [34] with a severity range from 8–56. High scores indicate a high level of fatigue. Patients with a cut-off score of ≥35 are classified as severely fatigued. This questionnaire has excellent psychometric properties, including good reliability and discriminative validity [35,36].

Secondary outcome measures are:

(1) Level of functional impairment measured with the Sickness Impact Profile (SIP) [37,38]. The SIP is an instrument that is used to gauge sickness-related dysfunction. The weighted total score on eight sub-scales of the SIP8 (SIP8 total score) will be used to assess functional disability in all domains of functioning. This instrument is reliable with sufficient content validity, and it shows good correlations with other health status and functional status measures [39].

(2) Level of psychological distress measured with the total score of the Symptom Checklist 90 (SCL90). The SCL90 consist of 90 items scored on a five-point scale. Scores range from 90–450. A low total score reflects psychological well-being. The SCL-90 is a reliable and valid instrument [40].

(3) *C. burnetii* serology (immunofluorescence assay; Focus Diagnostics, Inc., Cypress, CA, USA) and serum PCR.

Other study parameters will be: demographic data; data on symptoms, diagnosis and treatment of acute Q fever; previous history; serology results performed before inclusion in the study; use of medication, smoking, and the use of alcohol or drugs; and data on self reported symptoms, disabilities, and behavioral factors.

### Mediation analysis

Testing mediation is a strategy to identify variables that intervene in the relationship between treatment and outcome. Mediation analysis can help to better understand how treatment works [41]. To assess a change in variables that might affect fatigue severity, possible mediators and fatigue severity will be assessed at baseline, eight weeks after start of treatment, and at end of therapy in all treatment modalities (see Figure 1). The proposed mediators are fatigue related cognitions and behaviors. Four instruments will be used to assess the mediators: 1) Subscales ‘resting/avoidance’, ‘all-or-nothing’ behavior, and ‘catastrophising’ of the Cognitive Behavioral Responses to Symptoms Questionnaire (CBRSQ) [42], 2) Subscale focusing on symptoms of the Illness Management Questionnaire (IMQ) [43,44], 3) Total score on the Physical Activity Rating Scale (PARS, measuring the level of confidence and expectation on fatigue performing 16 different activities, rated on a five-point scale), and 4) Total score on the Self Efficacy Scale (SES28) [45].

### Withdrawal of individual participants

Participants are informed that they can stop participating in the study at any time, without consequences. Although participants will be asked for the reason for discontinuation, giving a reason for withdrawal is not obligatory. The investigator can decide to withdraw a participant from the study in case of medical urgency. In addition, study medication will be stopped in case of pregnancy, and the participant will be withdrawn. According to the Intention To Treat (ITT) principle the analysis will be based on the initial treatment intent. Therefore, in case of discontinuation, all efforts will be made to complete and report the observations as thoroughly as possible. A complete final evaluation in accordance to the study protocol end-of-therapy study visit will be performed if the withdrawn participant agrees. Because of absence of an evidence-based treatment for QFS, other treatment options for QFS in regular health care for withdrawn participants in the CBT group are not available. Long-term doxycycline treatment is not offered, because of possible (serious) side-effects and a lack of evidence so far.

### Adverse events

Adverse events are defined as any undesirable experience occurring to a subject during the study, whether or not considered related to the experimental treatment. All adverse events in the medication condition will be recorded during the pre-scheduled controls at the outpatient clinic, and, if applicable, during the trial if spontaneously reported by the participant. The most frequent side-effects of doxycycline include gastrointestinal complaints, like nausea and diarrhea, and photo-sensibilisation. Other side-effects are rare. The drug should not be given to children and to pregnant women. This RCT involves a non-critical indication for the use of doxycycline, and the drug under investigation is well characterised and commonly used in daily practice. Even though the delivery of CBT to adults is considered safe [46,47], all adverse events reported spontaneously by the participant or observed by the therapist will be recorded by the psychological assistant at pre-scheduled time-points during the therapy (8 weeks after the start of therapy, and 24 weeks after start of therapy). All adverse events will be followed until they have abated, or until a stable situation has been reached. If applicable, serious adverse events in both groups will be reported according to the principles of Good Clinical Practice (GCP).

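### Adverse events are collected under different rules in the CBT and medication arms, so CBT event rates cannot be compared with those on placebo or doxycycline

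*Protocol article*

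**What the plan says.** The Adverse events section of the protocol article opens with a definition that covers every participant: "Adverse events are defined as any undesirable experience occurring to a subject during the study, whether or not considered related to the experimental treatment". It then describes collection separately by treatment.

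- **Medication arms (doxycycline and placebo).** "All adverse events in the medication condition will be recorded during the pre-scheduled controls at the outpatient clinic, and, if applicable, during the trial" when the participant reports something spontaneously. The Study medication section sets the safety visits: these participants "will visit the Q fever outpatient clinic 4, 8, and 16 weeks after start of the treatment". It adds a laboratory check: "Furthermore, liver enzymes will be checked, and drug utilization will be recorded".
- **CBT arm.** After a remark that CBT in adults is regarded as safe, the rule is that "all adverse events reported spontaneously by the participant or observed by the therapist will be recorded by the psychological assistant", and this is done "at pre-scheduled time-points during the therapy (8 weeks after the start of therapy, and 24 weeks after start of therapy".

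Serious adverse events are to be reported under GCP in both groups. All participants attend the ECCF at week 24 and the outpatient clinic at week 26 (Post intervention).

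**The concern.** Under a single definition, a recorded event rate is the true rate multiplied by the chance that an event gets onto the form. If that chance differs by arm, recorded rates differ even when true harm is the same. Here the rule for CBT is narrower: an event counts only if the participant volunteers it or the therapist notices it, and the therapist is the unblinded person delivering the treatment. For the medication arms the rule is all events at the controls, with volunteered reports named as an addition. That wording implies that the visits are meant to pick up more than what is volunteered.

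Both active treatments are set against the same placebo arm, and the Discussion hopes to contribute to treatment guidelines. Adverse-event percentages for three arms printed side by side would be read as a comparison. A low CBT figure could then be taken as evidence of better tolerability when some or all of the difference came from how events were collected.

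**Working it through.** The plan states no figure on this point, so there is nothing to reproduce. The check sets the rules side by side and then shows how far unequal capture could move recorded rates.

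**Step 1: the rules compared** (Adverse events, Study medication, Cognitive behavioral therapy and Randomization sections)

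| | Doxycycline and placebo | CBT |
|---|---|---|
| Which events count | All, at scheduled controls, plus spontaneous reports | Volunteered, or observed by the therapist |
| Recording points | Safety visits at weeks 4, 8, 16 | Weeks 8, 24 |
| Longest gap between these points | 16 − 8 = 8 weeks | 24 − 8 = 16 weeks |
| Where or by whom | Q fever outpatient clinic | Psychological assistant, from participant or therapist |
| Liver enzymes | Checked | No counterpart described |
| Other contact | None described beyond these visits during treatment | 12–14 individual sessions over 24 weeks |
| Blinding | Double-blind between the two | Not possible |

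Doxycycline and placebo share one column, so their comparison is sound. Every comparison with CBT crosses columns.

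**Step 2: likely direction**

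The Cognitive behavioral therapy section describes sessions that challenge catastrophising beliefs about fatigue, train patients to turn their attention away from it, and increase activity on a timetable that does not follow symptoms. Patients taught this may volunteer fewer symptoms whether or not they have fewer. That points to lower capture on CBT. The number of sessions points the other way. So does the late schedule: CBT has a recording point at week 24, whereas the named medication safety visits end at week 16, and the article does not say whether the week-26 clinic visit counts as a control.

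**Step 3: possible size (all capture probabilities and true rates are assumptions)**

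Formula: recorded rate = true rate × capture probability. With equal true rates, the recorded ratio (CBT ÷ medication) = CBT capture ÷ medication capture, whatever the true rate.

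- 0.7 ÷ 0.9 = 0.78
- 0.5 ÷ 0.9 = 0.56
- 0.9 ÷ 0.7 = 1.29 (sign reversed)

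With 60 patients per arm (Study population), the chance of a nominally significant but spurious difference at two-sided 0.05 follows from the normal approximation for two proportions: Φ[(|p₁ − p₂| − 1.96·SE₀)/SE₁], with SE₀ pooled and SE₁ unpooled.

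| True rate, both arms | Capture, medication / CBT | Recorded, medication / CBT | Chance of spurious significance |
|---|---|---|---|
| 20% | 90% / 70% | 18% / 14% | 9% |
| 40% | 90% / 70% | 36% / 28% | 15% |
| 60% | 90% / 70% | 54% / 42% | 26% |
| 20% | 90% / 50% | 18% / 10% | 24% |
| 40% | 90% / 50% | 36% / 20% | 50% |
| 60% | 90% / 50% | 54% / 30% | 77% |

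Worked row (40%, 90% / 50%): p₁ = 0.40 × 0.9 = 0.36 and p₂ = 0.40 × 0.5 = 0.20. SE₀ = √(2 × 0.28 × 0.72 / 60) = 0.0820 and SE₁ = √[(0.36 × 0.64 + 0.20 × 0.80) / 60] = 0.0807. Then (0.16 − 0.1607) / 0.0807 ≈ −0.01, and Φ ≈ 0.50.

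**The case against.** The best reply has five parts.

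1. **No harm comparison is planned.** Adverse events are not among the primary or secondary outcomes, and the Statistical analysis section defines its contrasts for fatigue, then distress and functional limitations. This is correct, and tabulation is properly a matter for the full protocol or SAP. The collection rule, however, is fixed here and cannot be repaired at the analysis stage.
2. **CBT recording is scheduled too, and active questioning at the clinic is not stated.** Both are true. The contrast is not scheduled against unscheduled. It lies in which events count, who supplies them and when. Questioning at the controls is implied by the wording but not written down.
3. **CBT patients are seen far more often.** This stands as a reason for doubt about direction. It does not make the arms comparable.
4. **Worsening would be seen anyway.** Largely right for fatigue, which is measured at baseline, week 8 and end of therapy in all arms (Mediation analysis), and for function and distress, measured before and after treatment in all arms. Other undesirable experiences have no such common instrument.
5. **Extra visits for a drug are intrinsic to the design.** Accepted. They need not be removed, only kept out of comparisons with CBT.

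A reader might infer from the asymmetry that any harm comparison favours CBT by construction. The documents do not support that: they give no capture rates, do not state active questioning in the medication arms, and describe enough therapist contact for the sign to be reversed.

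**Conclusion.** The point holds as one of comparability. Under one adverse-event definition, the rules for CBT and for medication differ in source, recorder, timing and laboratory detection. CBT event rates therefore cannot be read against placebo or doxycycline. Under-recording on CBT is likelier than over-recording, but not certain. The size cannot be fixed from the article: over the assumed capture pairs the recorded ratio runs from 0.56 to 1.29 with no true difference, and the chance of a spurious significant result for 60 per arm runs from about 9% to 77%. Doxycycline versus placebo and the efficacy analyses are unaffected, and serious events follow the same reporting principle in both groups.

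**What to change.** - Put one standard, open adverse-event question, with the same recall period, to every participant at week 8 and week 24. At week 8, medication participants are asked at their existing outpatient visit and CBT participants at their existing recording point, by current staff other than the treating therapist. At week 24, all are asked at the shared ECCF visit. The article does not place the psychological assistant with medication patients at week 8, so the plan should not depend on one person asking everyone.
- Base any comparison involving CBT on the answers to this common question only.
- Report events and laboratory findings from the other medication visits for doxycycline versus placebo only.
- If the common question cannot be added, state that CBT events will be described and not compared with the medication arms.

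Cost: a few minutes at each of two existing contacts, with no new visits, and more recorded events on CBT. Different staff would still ask the question at week 8, and CBT participants remain unblinded, so the common set reduces the ascertainment difference without removing it.

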### Statistical analysis

The primary analysis will be the comparison between the experimental groups (CBT or doxycycline) and the placebo group. ITT will be the basis for all analysis. The primary analysis will be done on the data of completers. Completers are all participants who completed the post intervention measurements. When statistical significant differences are found, a sensitivity analysis will be performed on the basis of different assumptions about the values of missing data. To determine if there is a significant difference between the intervention arm and placebo condition, ANCOVA will be used with the outcome measure on the second assessment as dependent measure, the baseline score as covariate, and condition as fixed factor. A priori contrasts will be defined for the factor condition comparing CBT versus placebo, and comparing doxycycline versus placebo. For the secondary outcome measures, namely psychological distress and functional limitations, the same analysis will be repeated, but with the secondary outcome measures at the second assessment as dependent variable, and the scores at baseline as covariate. In this kind of trials ANCOVA yields greater power than other statistical methods [48]. Statistical significance will be assumed at *p* < 0.05 in all analysis. Data will be presented as quantitative results.

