### Power calculation

The power calculation is based on the estimated maximal number of eligible patients who will be available for the study. In the Netherlands there has been only one major outbreak of Q-fever. Since then, the number of new cases is limited. Furthermore, following the outbreak several studies investigating the symptoms following Q-fever are ongoing which limits the number of eligible patients that will be available to enter the present study. The maximal number of available patients is estimated to be 180, 60 patients for each arm of the study. We assumed a drop-out rate of 20 percent, leaving a sample size for the power calculation of 50 participants per arm. Compared to a *t*-test, using ANCOVA increases statistical power. The sample size of 50 can be divided by a design factor of 0.884 (1–0.34^2^), with 0.34 being the correlation between the CIS fatigue severity at baseline and second assessment [49]. The required effect size was estimated using G-Power 3.1.5. based on a sample size of 56, a power of 0.80 and an alpha of 0.05. The analysis showed that we need to assume a moderate controlled effect size of 0.53 to obtain a power of 0.8 for demonstrating a significant difference between the results in the treatment groups and in the placebo group.

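### The primary analysis is labelled ITT but omits randomised patients without an end-of-therapy score and leaves their week-8 fatigue scores unused, so arm-specific drop-out can bias both primary contrasts

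*Protocol article*

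**What the plan says.** The Statistical analysis section states: "ITT will be the basis for all analysis. The primary analysis will be done on the data of completers". It then defines the set: "Completers are all participants who completed the post intervention measurements". The model is a single-time-point analysis: "ANCOVA will be used with the outcome measure on the second assessment as dependent measure", with the baseline score as covariate, condition as fixed factor, and two contrasts against placebo. A sensitivity analysis under different assumptions about the missing values is promised, but only when a significant difference has been found.

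The section on withdrawal of participants says: "According to the Intention To Treat (ITT) principle the analysis will be based on the initial treatment intent". It also commits to completing observations after discontinuation, and says that a final evaluation "will be performed if the withdrawn participant agrees".

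The Mediation analysis section says that "possible mediators and fatigue severity will be assessed at baseline, eight weeks after start of treatment, and at end of therapy", in all treatment modalities.

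The Power calculation section says: "The maximal number of available patients is estimated to be 180, 60 patients for each arm of the study", and then: "We assumed a drop-out rate of 20 percent, leaving a sample size for the power calculation of 50 participants per arm".

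**The concern.** An ITT claim has two parts: patients are analysed in the arm to which they were randomised, and all randomised patients count. The plan meets the first part for everyone it analyses. It does not meet the second, because a patient without the end-of-therapy score contributes nothing to the primary contrast. The power calculation shows that this loss is planned.

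A complete-case ANCOVA is valid if, within each arm, missingness is unrelated to the outcome once baseline CIS is known. In this trial the arms can lose patients for different reasons. CBT is open-label (Randomization procedure and blinding). The medication arms have their own exclusion rules for side effects, liver enzymes, antibiotic use and interrupted medication (Study medication), and a broken code makes a participant ineligible. If these routes select patients by how fatigued they have become, the groups compared at week 24 are no longer the randomised groups. An effect can then be inflated, created or hidden. Yet the plan already collects a post-baseline measurement of the primary outcome that could explain part of such drop-out.

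**Working it through.** **The plan's own figures.**
- ANCOVA design factor: 1 − 0.34² = 0.884. Effective size: 50 / 0.884 = 56.5, used as 56.
- Detectable effect, two-sided alpha 0.05, power 0.80: (1.960 + 0.842) × √(2/56) = 0.529 by the normal approximation and 0.534 by the noncentral t. The stated 0.53 is reproduced, and it rests on 50 completers per arm.
- Planned loss: 20% of 60 is 12, leaving 48. The 50 used is a loss of 10/60 = 16.7%. Over three arms the primary analysis expects to omit 30 to 36 of 180.

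**How omission shifts the contrast.** Let π be the proportion missing in an arm, and δ the mean outcome of the missing minus that of the completers, given baseline. The completers' mean differs from the full-arm mean by −πδ, so the contrast shifts by −(π₁δ₁ − π₀δ₀).
- π = 0.20 in both arms, δ = 0.5 SD in both: shift 0.
- π = 0.20 in both arms, δ = 0.5 SD in one arm only: 0.20 × 0.5 = 0.10 SD, about a fifth of 0.53.
- π = 0.30 and 0.10, δ = 0.5 SD in both: (0.30 − 0.10) × 0.5 = 0.10 SD.

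**Simulation with no true effect.** From the documents: 60 per arm and a baseline to week-24 correlation of 0.34. Assumed: CIS SD 10; correlations of 0.5 (baseline to week 8) and 0.6 (week 8 to week 24); logistic drop-out of 24% depending on week-8 fatigue in one arm; 17% random drop-out in the other. There were 2,000 trials per row, so the simulation error of a 5% rate is about √(0.05 × 0.95 / 2000) = 0.5 percentage points.

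| Log-odds slope per SD of week-8 CIS | Bias of completers ANCOVA, CIS points | Type I error |
|---|---|---|
| 0.5 | 0.49 | 5.4% |
| 1.0 | 0.92 | 7.0% |
| 1.5 | 1.10 | 8.8% |
| 2.0 | 1.41 | 11.2% |

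The bias favours the arm that loses its most fatigued patients. Repeat runs agree within simulation error, with 5.4% to about 6% at the weakest slope. Imputation from baseline and week-8 CIS leaves a bias of about 0.05 points or less. Relative to the planned 0.53 SD (5.3 points at SD 10), the range is 0.49/5.3 = 9% to 1.41/5.3 = 27%.

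**When it does not matter.** With the same slope in both arms and 20% loss in each, there is no bias and type I error is about 5%. With the same slope but 24% against 17%, bias is at most about 0.4 points. Drop-out that depends only on baseline fatigue gives no bias.

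**With a true effect of 0.53 SD** (20% loss in each arm, slope 1, week-8 to week-24 correlation 0.4 to 0.75, half the effect present at week 8, large samples):
- Drop-out depends on week-8 fatigue in the active arm only: completers estimate 0.57 to 0.63.
- It depends on week-8 fatigue in opposite directions in the two arms: 0.61 to 0.73.
- In both cases the estimate that uses week-8 CIS returns 0.53.
- It depends on the unobserved week-24 score in the active arm only: completers 0.68 to 0.69; the week-8 estimate lowers this only to 0.61 to 0.67.

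**The case against.** A reader might infer that this is a per-protocol analysis. The documents do not support that. Being a completer depends on having the outcome measured and not on finishing treatment, and the withdrawal section seeks a final evaluation from those who stop. The plan is better described as an available-case analysis in the allocated arms. This stands, and it narrows the point to patients who do not return. The words used for exclusion under Study medication, and for ineligibility after a broken code, do blur whether those patients are still followed and analysed.

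A reader might also infer that any link between drop-out and fatigue causes bias. It does not: baseline adjustment deals with drop-out related to baseline fatigue, and drop-out acting identically in both arms cancels.

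The upper type I error needs a strong dependence in one arm and none in the other. A slope of 1.5 to 2 is an odds ratio of about 4.5 to 7 per SD. The documents give no drop-out by arm, so 11% is an adverse case and not a forecast.

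The plan does provide a sensitivity analysis, and its trigger covers the false-positive case. It does not cover a null result, which differential drop-out can also produce, and its assumptions are not named.

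Finally, the label for the dependent variable could be read as week 8, which is literally the second CIS measurement. The Abstract, the Post intervention section and the definition of completers make week 24 clear, so naming the week is only an editorial improvement.

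This is not a matter left to an unseen analysis plan: the article itself fixes the primary analysis set.

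**Conclusion.** The point holds in this limited form. The ITT label and the primary analysis set do not agree for patients without an end-of-therapy score, who are expected to be 30 to 36 of 180, and the week-8 CIS collected in all arms is left out of the primary model. The consequence is conditional. Bias arises when drop-out depends on post-baseline fatigue differently by arm, or at different rates. That is plausible given an open-label CBT arm and exclusion rules specific to medication, but the documents do not show that it will happen. Under the assumed values the bias is about 0.5 to 1.4 CIS points (0.05 to 0.14 SD) and type I error about 6% to 11%; it is essentially nil when drop-out is alike in the arms. The SD, the correlations with week 8, the arm-specific loss and the strength of dependence are all assumptions. The existing sensitivity analysis does not remove the problem, because it is conditional on significance.

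**What to change.** - Define the primary analysis on all randomised patients in their allocated arm. Use a likelihood-based repeated-measures model of CIS at weeks 8 and 24, with baseline CIS by visit, condition by visit and unstructured covariance, and the same two contrasts against placebo at week 24. Multiple imputation that includes week-8 CIS, followed by the planned ANCOVA, is an acceptable alternative. It also carries patients with neither post-baseline score, who would drop out of a model that has baseline only as a covariate.
- Run missing-not-at-random sensitivity analyses whatever the primary result, with the assumptions named in advance. The week-8 score only partly corrects drop-out driven by the unseen week-24 score.
- Keep the completers ANCOVA as a supportive analysis, described as such.
- Name week 24 as the time point of the dependent variable.
- Reconcile the exclusion and ineligibility wording with the withdrawal section, so that it is clear whether these patients remain in follow-up and in the analysis. This concerns the analysis set only and not the clinical rules.

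The cost is analysis wording and a little more analysis work, with no new visits, data or patients. The new primary analysis relies on missing at random given baseline and week-8 fatigue, which is a weaker assumption than the one the completers analysis makes.
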